#### Exposure measures

2.4.1

##### Assessment, care, and trust – in pregnant and new mothers

2.4.1.1

At baseline, all participants will be assessed using the Assessment, Care, and Trust in Pregnant and New Mothers (ACT-PNM) questionnaire developed by Rodríguez-Muñoz et al. (86). This 40-item instrument collects demographic and background information and assesses war-related experiences. To ensure applicability across all study cohorts, the questionnaire was slightly modified for use with women’s partners and non-pregnant women. Data derived from this measure will be used to describe the study sample and examined as potential covariates in further analyses. Where relevant, selected war-related items will be repeated at follow-up assessments to capture changes in participants’ living circumstances over time in the context of ongoing war. A psychometric evaluation of the questionnaire is not required, because the instrument was designed to capture a broad range of living and reproductive experiences in wartime Ukraine and not to measure a single latent construct or generate a unified scale score (86).

War-related stressor exposure will be assessed using predefined ACT-PNM indicators reflecting discrete wartime experiences and living conditions. For the primary analysis, war-related stressor burden will be operationalized as the number of endorsed stressor domains at baseline, with higher values indicating exposure to a broader range of war-related stressors. The predefined domains will include displacement, separation from a partner or close family members, disruption of healthcare access, economic hardship, proximity to hostilities or unsafe living conditions, and direct or indirect exposure to threat, injury, death, or war-related attacks. Domain-specific indicators will also be retained for secondary analyses to examine whether forms of exposure are differentially associated with mental-health trajectories.

Because exposure may change during ongoing war, selected ACT-PNM indicators will be reassessed at follow-up waves where applicable. In secondary longitudinal analyses, time-updated war-related stressor burden will be modeled as a time-varying exposure, defined as the cumulative number of stressor domains reported up to each assessment point. These analyses will be interpreted as secondary because war-related circumstances and psychological symptoms may change concurrently during follow-up. The IES-R will not be used to define war-related exposure, as it measures trauma-related symptom severity rather than exposure itself.

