Item-level analyses will include inspection of response distribution and missingness, floor and ceiling effects, corrected item-total correlations, and score distributions. For measures administered at multiple assessment waves, longitudinal measurement invariance will be evaluated to assess whether the constructs are measured comparably over time. Invariance by respondent characteristics or reproductive status will be examined where item wording, sample size, and model stability permit. Configural, metric, and scalar invariance will be examined sequentially; partial invariance will be considered when full invariance is not supported (146).

The results of these analyses will inform the interpretation of scale scores, between-group comparisons, and longitudinal change estimates. If a translated scale demonstrates poor psychometric performance, substantive analyses using that scale will be reconsidered before interpretation. The research team will inspect item wording, response distributions, factor loadings, residual correlations, reliability estimates, and the effect of individual items on model fit and internal consistency. Depending on the source and extent of the problem, analyses may use theoretically justified subscale scores, conduct sensitivity analyses excluding items, or report the measure descriptively. Measures with inadequate reliability, unstable factor structure, or insufficient evidence of comparability across groups or time will not be used. Any deviations from the planned scoring approach will be reported transparently.

Primary outcomes will be analyzed using mixed-effects growth models with repeated observations nested within participants. Models will include fixed effects for time, war-related stress exposure, and the interaction between them. Time will initially be modeled as categorical; alternative specifications will be compared when empirically justified. Random intercepts will be used to estimate between-person differences in baseline symptom levels, and random slopes for time will be tested to capture heterogeneity in change over time. Model selection will be guided by likelihood-ratio tests, Akaike information criterion, Bayesian information criterion, convergence diagnostics, and variance estimates. The intraclass correlation coefficient will be estimated from unconditional models.

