For postpartum participants, time since childbirth will be incorporated into the analytic framework to account for heterogeneity within the first postpartum year. Postpartum timing will first be described continuously in months since childbirth and, where sample size permits, also examined using clinically meaningful intervals, such as early versus later postpartum periods. In longitudinal models, postpartum timing will be considered as an adjustment variable, a time-varying covariate, or a basis for sensitivity or stratified analyses, depending on the distribution of observations and model stability.

Adjusted models will include selected sociodemographic, obstetric, clinical, and contextual covariates. For time-varying predictors, person-mean centering will be used to distinguish within-person from between-person effects (147). Moderation by risk or protective factors, such as displacement status, prior mental health history, socioeconomic status, social support, and reproductive status, will be tested using interaction terms. Results will be reported as model-based estimates with 95% confidence intervals, p-values, standardized effect estimates, marginal and conditional R², estimated marginal means, contrasts, and predicted trajectory plots. Interpretation will prioritize effect sizes, clinical relevance, and robustness across sensitivity analyses.

To reduce the risk of false-positive findings and model overfitting, the primary analytic model will follow a prespecified hierarchy. The primary longitudinal analysis will focus on WHO-5 trajectories, with baseline war-related stressor burden as the main exposure and the stressor burden-by-time interaction as the principal test of the primary hypothesis, with baseline-to-12-month change treated as the principal longitudinal contrast. Baseline reproductive status will be included to account for cohort-entry differences. Data-driven stepwise selection will not be used for primary inference. For tests conducted across the primary outcome family, Holm-adjusted p-values will be reported alongside unadjusted estimates.

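### Person-mean centring a cumulative stressor count ties both the between-person and within-person terms to retention (secondary time-updated exposure analysis)

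*Protocol article*

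**What the plan says.** Section 2.4.1.1 of the protocol article sets up two exposure variables. The primary one is fixed at entry: "war-related stressor burden will be operationalized as the number of endorsed stressor domains at baseline". The second is updated over follow-up and enters the secondary models as a time-varying exposure. It is a running total, "defined as the cumulative number of stressor domains reported up to each assessment point". The same section gives the reason for re-asking: "selected war-related items will be repeated at follow-up assessments to capture changes in participants’ living circumstances over time".

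Section 2.5 (Data analysis) then states a general rule: "For time-varying predictors, person-mean centering will be used to distinguish within-person from between-person effects". Neither section exempts the cumulative count.

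For the growth models of the primary outcomes, Section 2.5 says "Models will include fixed effects for time, war-related stress exposure, and the interaction between them". On the form that time takes in those models, it adds: "Time will initially be modeled as categorical; alternative specifications will be compared when empirically justified". Section 2.5 also expects that displacement, distress and access to care may influence who stays in follow-up, and it plans estimation under a missing-at-random assumption.

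**The concern.** Person-mean centring splits a predictor into a stable personal level and a deviation from it. That works when the predictor moves up and down around a level. A count of domains reported so far only rises or stays flat, so its average is partly a record of how long the woman was observed.

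Two consequences follow. First, two women with the same exposure process get different between-person burdens if one leaves early. Second, the deviation at any given wave depends on whether later waves were completed. If leaving depends on earlier well-being, the centred predictor carries information about the outcome through dropout. The likelihood's protection under missing-at-random assumes covariates that do not themselves encode the dropout time, and here one does.

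At stake is the reading of the only time-updated war exposure that the article defines. The within-person artefact, when women with lower well-being leave, points the way the study hypothesis does: more stressors, worse well-being.

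**Working it through.** The plan gives no figure for this analysis, so there is none to reproduce. The check is algebra, then simulation.

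**Inputs.** From the article: six stressor domains (Section 2.4.1.1), four waves, and 12-month retention of 0.730 (main) or 0.52 (conservative) (Section 2.2.1). Assumed, because the article does not give them: mean baseline count 2.4, and a probability h = 5%, 10% or 20% per wave that a domain not yet reported is added.

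**Step 1: person mean by number of waves attended.** The expected count at wave k (k = 0 to 3) is 6 - 3.6 × (1 - h)^k. For h = 10% this gives 2.40, 2.76, 3.08 and 3.38. Averaging over the waves attended:

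| h | 1 wave | 2 waves | 3 waves | 4 waves |
|---|---|---|---|---|
| 5% | 2.40 | 2.49 | 2.58 | 2.66 |
| 10% | 2.40 | 2.58 | 2.75 | 2.90 |
| 20% | 2.40 | 2.76 | 3.07 | 3.34 |

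Simulation at the main retention gave the same pattern: 2.41 to 2.67, 2.37 to 2.90 and 2.40 to 3.34 from one to four waves. The exposure process is identical along each row.

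**Step 2: how dropout enters the within-person term.** Take the baseline observation with h = 10%. Its expected centred value is 2.40 minus the person mean: 0.00 for a woman seen once, -0.18 for two waves, -0.35 for three, -0.50 for four. Same wave, same expected count, but a higher centred value for the woman who leaves. If low scorers leave, high centred values pair with low scores.

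**Step 3: link with wave.** Wave indicators explain 23%, 37% and 51% of the variance of the centred count for the three values of h. Variance inflation is 1/(1 - R²): 1.30, 1.58 and 2.04. The standard error grows by the square root, about 1.14 to 1.43.

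**Step 4: size of the bias.** Simulated 12,000 women per setting. True exposure effect zero, random-intercept SD 0.6 and residual SD 0.8 (total variance 0.36 + 0.64 = 1), common trend -0.1 SD per wave. Dropout was either random or had logit -2.3 - 1.0 × last observed score, so each SD of lower well-being multiplies the odds of leaving by e, about 2.7. In the second case 12-month retention was about 0.66, between the plan's two scenarios. All models are random-intercept models with categorical wave. Coefficients are in SD per domain:

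| Dropout | Term | h = 5% | h = 10% | h = 20% |
|---|---|---|---|---|
| Random | centred count | -0.006 | -0.012 | +0.007 |
| On last score | centred count | -0.102 | -0.098 | -0.081 |
| On last score | person mean | +0.010 | +0.013 | +0.043 |
| On last score | change from baseline | -0.020 | -0.018 | +0.003 |
| On last score | baseline count | 0.000 | -0.005 | +0.003 |

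Standard errors are 0.007 to 0.013 for the centred count, 0.004 to 0.005 for the person mean, and 0.006 to 0.011 for change from baseline. A separate simulation gave -0.07 to -0.09 for the centred count and +0.02 to +0.07 for the person mean. With outcome-related dropout, the centred count misses zero by many standard errors. The baseline-plus-change split of the same count stays close to zero; its largest departure is a little over two standard errors (-0.018, SE 0.008).

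**The case against.** **The cumulative count is deliberate.** The Introduction adopts an allostatic-load view and calls for a cumulative-exposure framework, so a count of domains ever reported fits the theory. This stands. A reader might infer that the count itself is wrong because it cannot register return from displacement or restored care, and that it should be replaced by a current count. The documents do not support that. If accumulation drives the outcome at a true -3.0 WHO-5 points per domain, a current count recovers only -1.19 to -1.42 in simulation (persistence of domains 50% to 85%). For the same reason one cannot say that the planned within-person estimate is attenuated: that holds only if current exposure is assumed to drive the outcome. The fault is in the centring.

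**Wave is in the model.** A reader might also infer that the within-person effect is confounded with time. Leaving wave out does produce false effects of -0.155, -0.125 and -0.089 SD per domain under random dropout. But Section 2.5 specifies time as a fixed effect, at first categorical, and with it those effects vanish (Step 4, first row). Collinearity and some loss of precision remain.

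**The combination is inferred.** The centring sentence is generic, Section 2.4.1.1 does not mention centring, and an analysis plan that is not shown could make an exception. That is fair. Still, the article calls this burden time-varying and states the rule for time-varying predictors without qualification, so the plain reading applies it.

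**The contrast uses extremes.** Only 7.1% of women are seen once under the main retention (1 - 0.929), and the between-person artefact is small. This stands for the between-person term. It does not answer the within-person bias.

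**Conclusion.** The point holds for a secondary analysis. That the person mean depends on the number of waves attended needs no assumption beyond some accrual of domains during follow-up; its size (2.4 against 2.7 to 3.3) rests on the assumed accrual. If a domain is not re-asked at follow-up it cannot accrue, and the artefact shrinks.

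The within-person bias of about -0.07 to -0.10 SD per domain, and the between-person bias of about +0.01 to +0.07, further require dropout related to earlier well-being. The article regards this as possible but gives no strength for it. Under random dropout the within-person bias is absent. The sign follows from assuming that women with lower well-being leave; the reverse pattern would reverse it.

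A reader might infer that the main result is in doubt. It is not: the primary test uses the baseline count, which is neither cumulative over follow-up nor centred within person.

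**What to change.** State in Section 2.5 that the cumulative burden is exempt from person-mean centring. Enter it as two terms, baseline burden and uncentred new domains since baseline, and keep categorical wave in the model. Describe the second term as the association with domains added since baseline. It should not be called a pure within-person effect, because women also differ in how fast they accrue domains.

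Optionally, add a sensitivity analysis with a person-mean-centred count of domains present at each wave, since the cumulative count cannot show relief. This is possible only where the repeated items allow it: the article says that a selection is re-asked and does not give their recall period.

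The main change costs a few sentences of analysis wording and uses the same data. The optional analysis may need the follow-up items checked before launch.

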##### Impact of events scale – revised

2.4.1.2

The Impact of Event Scale – Revised (IES-R) is a self-report questionnaire used to assess trauma-related symptoms following exposure to a traumatic event (92). The instrument comprises 22 items, rated on a 5-point Likert scale from 1 to 5, with higher scores indicating greater trauma-related symptom severity and a cut-off score of 30 indicating a high probability of a trauma-related disorder. The scale has been widely used in perinatal populations to assess distress in the context of the COVID-19 pandemic (93–95) as well as disasters (96). The validated Ukrainian version of the measure will be used in the present study (97).

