City BiTS (Partner Version)	Webb et al. (2021) (126)	—	29	Likert scale (0–3)	2/4	2-factor: Birth-related symptoms; general symptoms. 4-factor: Re-experiencing; avoidance; negative cognitions and mood; hyperarousal	0–60	—
BSS-R	Martin & Martin (2014) (130)	—	10	Likert scale (0–4)	3	Quality of care provision; women’s personal attributes; stress experienced during labor	0–40	—
DAP	Rocca et al. (2019) (118)	—	14	Likert scale (0–4)	3	Cognitive desires and preferences; affective feelings and attitudes; anticipated practical consequences	0–4	—
LMUP	Barrett et al. (2004) (121)	—	6	0–2	1	Unidimensional	0–12	—
MSP/PSP	Jawed-Wessel et al. (2016) (135)	—	MSP: 6 PSP: 8	Likert scale (1–6)	1	Unidimensional	1–6	—
MASQ	Patrick et al. (2011) (138)	—	9	Likert scale (1–5)	3	Values; health; not ready	1–5	—
DVMAS	Peters (2008) (139)	—	18	Likert scale (1–7)	4	Minimization; exoneration; behavior blame; character blame	1–7	—
GAD-7	Spitzer et al. (2006) (112)	Aleksina et al. (2024) (115)	7	Likert scale (0–3)	1	Unidimensional	0–21	7
IES-R	Weiss & Marmar (1997) (92)	Krupelnytska et al. (2025) (97)	22	Likert scale (1–5)	3	intrusion; avoidance; hyperarousal	22–110	30
SCI-2-SF	De Luca et al. (2024) (116)	Yatsenko et al. (2024) (117)	9	Likert scale (0–4)	5	Entrapment; affective disturbance; loss of cognitive control; hyperarousal; social withdrawal	0–4	—
ACE	Felitti et al. (1998)	Lotzin et al. (2023) (73)	10	Dichotomous	N/A	N/A	0–10	N/A

*, raw WHO-5 multiplied by 4 to obtain standardized score ranging from 0 to 100; the cut-off value of 50 refers to the transformed 0–100 score.

**Table 2 T2:** Psychometric evidence for the study measures.

Measure	Version	Validation source	Internal consistency	Test–retest/procedural reliability	Item-level evidence	Factor structure/model fit	Validity/diagnostic accuracy
WHO-5	Original	World Health Organization (1998) (100)	α = .84	Not reported	Not reported	Loevinger’s H = .56	Not reported
EPDS	Original	Cox et al. (1987) (104)	α = .87; split-half reliability = .88	Not reported	Not reported	Not reported	Sensitivity = .86; specificity = .78; PPV = .73
	Ukrainian	Chrzan-Dętkoś et al. (2026) (111)	α = .86–.87; subscale α = .73–.85	Not reported	Item-total r = .35–.73	CFA: χ²(32) = 55.34–79.29, CFI = .97, TLI = .96, RMSEA = .06, SRMR = .04	Convergent validity: r = .44–.72

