An automated safety-response pathway will be embedded in the web-based questionnaire. The pathway will be activated by predefined thresholds for possible acute risk or clinically elevated distress, including an SCI-2-SF score of ≥ 2, EPDS ≥ 13, GAD-7 ≥ 7, IES-R ≥ 30, or City BiTS ≥ 29. When activated, the questionnaire will immediately display a neutral safety message, information on crisis and psychosocial support services, instructions to contact emergency services or the nearest healthcare facility if immediate danger is present, and options to stop, pause, or continue the questionnaire. After receiving the safety message, participants will retain control over their participation. They may stop the questionnaire, pause and return later, skip any item, or continue if they consider it safe and acceptable. The message will also remind participants that participation is voluntary, and that non-completion or withdrawal will have no consequences for their medical care or access to services. All participants, regardless of whether the safety pathway is activated, will receive mental-health and crisis-support information at the end of the questionnaire.

The automated response will not generate notifications to partners, accompanying persons, or routine clinical staff. Where the participant has provided consent for follow-up contact and has indicated a safe contact method, a trained member of the research team may review the alert according to the approved safety protocol and provide information on available referral pathways. The study team will not provide clinical diagnosis, psychotherapy, emergency monitoring, or real-time crisis intervention as part of the study. Because data are collected through a web-based, pseudonymized questionnaire and responses are not monitored continuously in real time, the study team cannot guarantee individualized emergency response to each risk-related answer. For this reason, the primary safety mechanism is the immediate automated provision of emergency, crisis, and referral information within the survey itself. If a participant independently contacts the research team and reports acute distress, suicidal intent, or risk of self-harm, a trained member of the research team will respond within one day.

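### The IES-R cut-off and safety trigger of 30 sit only 8 points above the lowest possible score under the stated 1–5 item coding

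*Protocol article*

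**What the plan says.** Three places in the protocol article bear on this.

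- **Section 2.4.1.2 (Impact of events scale – revised)** gives the coding: "The instrument comprises 22 items, rated on a 5-point Likert scale from 1 to 5". Higher scores mean more severe symptoms. The same sentence sets the threshold, "a cut-off score of 30 indicating a high probability of a trauma-related disorder".
- **Table 1** repeats the 1–5 response format and the cut-off of 30, and gives a score range of 22–110.
- **Section 2.6.1 (Ethical considerations)** describes the automated safety pathway: "The pathway will be activated by predefined thresholds for possible acute risk or clinically elevated distress". The list of thresholds follows, "including an SCI-2-SF score of ≥ 2, EPDS ≥ 13, GAD-7 ≥ 7, IES-R ≥ 30, or City BiTS ≥ 29".

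Nowhere is the IES-R rescaled, shifted to start at zero, or given a second coding. For the WHO-5, by contrast, the Table 1 footnote says which metric applies: "the cut-off value of 50 refers to the transformed 0–100 score". The IES-R row has no such note.

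Table 3 schedules the IES-R for all three cohorts of women and for partners at all four waves.

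**The concern.** A total built from 22 items scored at least 1 cannot fall below 22. On that metric 30 is close to the floor, yet the article treats it as marking a probable trauma-related disorder and as a reason to activate a pathway meant for acute risk or elevated distress. Few mild answers are needed to cross it.

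What is at stake is how well the safety pathway discriminates. If the trigger fires for women with minimal symptoms, the alert says little about who is distressed, and any team review of alerts takes on extra load. This matters most for non-pregnant women. Table 3 gives them neither the EPDS nor the City BiTS, so of the five thresholds listed only the SCI-2-SF, the GAD-7 and the IES-R can apply to them. Anyone who later classified respondents with the stated cut-off would also label minimal symptoms as probable disorder.

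**Working it through.** **Inputs.** 22 items coded 1–5 and cut-off 30 (section 2.4.1.2 and Table 1); range 22–110 (Table 1); trigger at 30 or more (section 2.6.1).

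**Step 1: reproduce the stated range.** Minimum = 22 × 1 = 22. Maximum = 22 × 5 = 110. This matches Table 1, so the score is a plain sum with a floor of 22, and the 1–5 coding is not a slip in one place.

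**Step 2: locate the cut-off.**
- Distance from the floor: 30 − 22 = 8 points.
- Share of the range: 8 / (110 − 22) = 8/88 = 9.1%.
- Mean item score at the cut-off: 30/22 = 1.36, where 1 is the lowest answer.
- A response pattern that reaches it: 8 × 2 + 14 × 1 = 30.

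The response anchors are not printed. That the lowest answer means no symptom is inferred from higher scores meaning greater severity.

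**Step 3: compare with the other listed triggers**, using (cut-off − minimum)/(maximum − minimum) and the Table 1 ranges.

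| Scale | Range | Trigger | Position in range |
|---|---|---|---|
| EPDS | 0–30 | 13 | 43% |
| GAD-7 | 0–21 | 7 | 33% |
| City BiTS | 0–60 | 29 | 48% |
| SCI-2-SF | 0–4 | 2 | 50% |
| IES-R as written | 22–110 | 30 | 9% |
| IES-R if coded 0–4 | 0–88 | 30 | 34% |

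The IES-R is the only trigger scale with a non-zero floor. Read as a zero-based cut-off, 30 would fall in line with the rest. This suggests a mismatch of metrics but does not prove which element is wrong.

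**Step 4: the equivalent cut-off on 1–5 coding.** If 30 belongs to a zero-based total, add one point per item: 30 + 22 = 52. Its position is (52 − 22)/88 = 34%, with a mean item score of 52/22 = 2.36.

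**Step 5: how often the trigger might fire (illustration only).** The article gives no IES-R distribution. Assume that the total minus 22 is beta-binomial on 0–88 with the mean and SD shown. The trigger as written then fires when this zero-based total is 8 or more; a trigger at 52 fires when it is 30 or more.

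| Assumed mean (zero-based) | Assumed SD | Flagged at 30 as written | Flagged at 52 |
|---|---|---|---|
| 10 | 10 | 0.48 | 0.06 |
| 10 | 15 | 0.36 | 0.11 |
| 20 | 10 | 0.91 | 0.17 |
| 20 | 15 | 0.77 | 0.24 |
| 30 | 10 | 0.996 | 0.50 |
| 30 | 15 | 0.95 | 0.48 |

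A cruder illustration allows only the two lowest answers. If each item is independently a 2 with probability 0.3, 0.4 or 0.5 and otherwise a 1, the chance of at least 8 twos among 22 items is 33%, 71% or 93%. No respondent in that model ever goes beyond the second-lowest answer.

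**The case against.** The strongest reply is that over-firing does little harm. The message is neutral, nobody outside the study is notified, and support information goes to everyone anyway: "All participants, regardless of whether the safety pathway is activated, will receive mental-health and crisis-support information at the end of the questionnaire". Staff involvement is discretionary, since "a trained member of the research team may review the alert according to the approved safety protocol", and then only with consent to follow-up contact and a safe contact method. A lenient threshold misses no one. Section 2.5 uses no IES-R caseness, section 2.4.1.1 bars the scale from defining exposure, and the team makes no diagnosis. All of this stands, and it limits the consequence to a less specific alert, possible review workload, and a printed cut-off that would mislead anyone who used it.

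A second reply is that the flagged shares rest on assumed distributions. That is right: a range from 36% to 99.6% shows direction, not a prediction. The 8-point distance is exact and carries the point alone.

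Third, the value 52 depends on an unverified origin of the cut-off, and the trigger list opens with a word that leaves it non-exhaustive. Both are fair. The first is why the remedy starts with the source; the second means that three triggers for non-pregnant women is a count of those listed.

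None of these replies reconciles the coding with the cut-off. Nor can the matter be left to a fuller document, because coding, range, cut-off and trigger are all stated here and conflict.

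**Conclusion.** The concern holds. As written, the IES-R threshold lies 8 points, or 9.1% of the range, above the lowest possible score. It cannot credibly mark a probable disorder or elevated distress. That conclusion rests only on figures in the article, plus the reasonable reading that the lowest answer means no symptom.

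The share of respondents flagged is unknown. Under the assumptions above, at a zero-based mean of 20 it would be about 77–91% as written, against 17–24% with the cut-off 30 points above the floor.

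The error is over-inclusive and confined to the safety trigger and the stated cut-off. The WHO-5 primary analysis, the sample size of 328 and the planned models are unaffected. It should be fixed because it is a mis-set rule in a participant-safety procedure and is cheap to correct before launch.

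**What to change.** Before launch, go back to the source that set the cut-off and establish the item coding it used. Then put coding, range and cut-off on that one metric, and correct Table 1, section 2.4.1.2 and the trigger in section 2.6.1 together.

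If the source used a zero-based total, which has to be checked, there are two equivalent choices:
- code items 0–4, with range 0–88 and cut-off 30; or
- keep 1–5 coding, with range 22–110 and cut-off 52.

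Add a Table 1 footnote stating the metric of the IES-R cut-off, as is done for the WHO-5, and confirm that the rule programmed in the survey platform uses the same coding.

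The cost is one table row, one sentence and one survey rule. Sample size and primary analysis do not change.
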